
## Discussion

Exposure to childhood adversity may have deleterious effects on self-esteem, which, in turn, has been shown to be an important putative transdiagnostic mechanism in pathways from childhood adversity to adult psychopathology [37, 38] and, thus, is a promising target for early intervention. Even though self-esteem is a common target of conventional psychological interventions [51, 71, 72, 101], current psychological help remains difficult to access for youth in real-world service delivery settings [49, 50], and therefore, new approaches are required. The current paper presents the study protocol of a multi-center RCT to evaluate the efficacy of an EMI (SELFIE) to improve self-esteem in youth exposed to childhood adversity. SELFIE, an intervention that extends beyond or even outside the clinical setting, has been designed to improve the accessibility and efficacy of psychological interventions for youth exposed to childhood adversity [49, 50]. The potential effects of the SELFIE intervention may help to minimize the deleterious impact of, and hence, resilience to, childhood adversity by improving self-esteem and, thereby, prevent the development of severe and enduring mental disorder later in life and reduce disease burden. This study contains several unique and novel aspects. To our knowledge, SELFIE is the first transdiagnostic EMI that focuses on improving self-esteem in youth exposed to childhood adversity, which will inform our understanding of self-esteem as a psychological mechanism as well as the growing knowledge of mHealth intervention development and implementation, in particular for EMIs. An advantage of EMIs is that the intervention components are delivered in, and therefore more easily translated to, diverse contexts of daily life [54]. In doing so, the SELFIE intervention focuses on positive rather than negative self-esteem, that is, the goal of SELFIE is to build a competing positive self-esteem, without directly targeting more deeply rooted negative self-esteem [72]. This makes this low-level intervention suitable as a guided self-help EMI that is easily accessible, individually tailored and offered in daily life. Also, the multi-center RCT design implemented in different regions of the Netherlands will provide high external validity of findings. Cost effectiveness and cost utility will inform implementation, and the process evaluation on acceptability, treatment adherence, and treatment fidelity will provide important data on potential barriers, but also on potential facilitators for implementation.

## Trial status

The trial has been registered at trialregister.nl (no. NTR 7475) in November 2018, and all study procedures were approved by the MERC at MUMC in August 2018. We are currently working with protocol version 10, originating from February 2021. Recruitment started in December 2018, the first enrollment was in January 2019, recruitment was completed in June 2021, and outcome assessment will continue until December 2022.

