## Methods

### Study design

In a two-arm parallel-group, assessor-blind multi-center randomized controlled trial, individuals aged between 12 and 26 years with prior exposure to childhood adversity and low self-esteem will be randomly allocated to SELFIE in addition to TAU as the experimental condition or a control condition of TAU only, which includes (access to) standard health care and social services. Participants will be recruited from mental health services in Noord-Holland, Zuid-Holland, and Limburg (the Netherlands) and from the general population (e.g., via social media). Outcomes will be measured at baseline (i.e., before randomization), post-intervention (i.e., after the 6-week intervention period), and 6-month, 18-month, and 24-month follow-up (i.e., 6, 18 and 24 months after completing the intervention period) by blind assessors (see Figs. 1 and 2). Randomization will be conducted independently of the research team through a computer-generated sequence, stratified by region of collaborating centers or as external admission. All outcomes will be measured and the statistical analysis will be performed blind to treatment allocation.

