### Sample size

Previous studies demonstrated that third-wave cognitive behavioral therapy (CBT) [22, 99, 100], including CBT focusing on self-esteem [51, 101], may lead to reductions in symptoms of psychopathology of moderate to large effect size. In line with previous research, the power calculation is based on the primary outcome of level of self-esteem as measured with the RSES [51]. Power simulation in the R environment indicated that a sample size of 130 participants (65 per condition) is sufficient to test our primary hypothesis of the effect of condition (SELFIE + TAU vs. TAU) on self-esteem, while controlling for self-esteem at baseline. Specifically, this will allow us to detect an effect size (standardized mean difference (SMD)) of 0.3 (experimental vs. control condition), i.e., a difference that is considered clinically relevant, at (at least) post-intervention or 6-month follow-up with a power of 0.87 (primary hypothesis), and, at long term, (at least) at one of the post-intervention and follow-up time points (6-month, 18-month, and 24-month follow-up), with a power of 0.82 when testing at alpha = 0.05 using linear mixed modeling. Based on our previous and ongoing work, we will allow for a 25% attrition rate at 2-year follow-up, which will result in a loss to follow-up of around 22 individuals per condition on average (see Fig. 1). Hence, we will recruit a total sample of 174 participants (87 experimental, 87 control condition) at baseline.

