### Statistical analysis

A full statistical analysis plan will be written and published prior to unblinding of the study and before any analysis is being undertaken. The trial data set will be accessed by the investigators to test the primary hypothesis of an improvement in self-esteem at post-intervention and 6-month follow-up in a priori planned statistical analysis when data collection for assessments at 6-month follow-up has been completed while retaining masking of assessors until the last assessment of the last participant at 24-month follow-up. We will use a linear regression model with the primary outcome of self-esteem at post-intervention and 6-month follow-up entered as the dependent variable and self-esteem measured at baseline, condition (SELFIE + TAU vs. TAU), time (as a two-level factor), center (as a four-level factor), the baseline × time interaction, and a time × condition interaction term as independent variables, in line with the intention-to-treat principle. All randomized participants will be included in the analysis and will be analyzed according to the intention to treat principle. Residuals within subjects will be allowed to be correlated with a completely unstructured variance-covariance matrix to take within-subject clustering of repeated measures into account. We will fit the model using Restricted Maximum Likelihood (REML [102]) in Stata 15 [103], which allows for all available data to be used assuming that data is missing at random if all variables associated with missing values are included in the model [104, 105]. Therefore, potential bias due to attrition over the study period, differences between centers, or as a function of baseline self-esteem will be minimized by the model. We will make every effort to assess all participants at post-intervention and follow-up. To test the main effect of condition, an omnibus test of no difference between the two conditions at all two time points (Wald-type test with df = 2 and alpha = .05) will be used. The two time-specific contrasts will be examined if the omnibus test is statistically significant to determine at which time points significant differences are present (each tested at alpha = .05). The two time-specific contrasts (to determine at which time points significant differences are present) will only be examined if the omnibus test is significant and, hence, the family-wise type I error rate of finding at least one significant difference at the three time points is controlled at alpha = .05. Hypotheses in relation to secondary outcomes of momentary self-esteem, positive and negative schematic beliefs of self, resilience, emotional well-being, general psychopathology, functioning, and quality of life at post-intervention and 6-month follow-up will be tested following the same steps. The investigators will access the trial data set to test hypotheses in relation to all four time points (i.e., post-intervention, 6-month, 18-month, and 24-month follow-up) in a priori planned statistical analysis when data collection for assessments at 24-month follow-up has been completed. For hypotheses in relation to primary and secondary outcomes at all four time points (i.e., post-intervention, 6-month, 18-month, and 24-month follow-up), the main effect of condition will be tested using, again, an omnibus test of no difference between the two groups at all four time points (Wald-type test with df = 4 and alpha = .05). The four time-specific contrasts will be examined to determine at which time points significant differences are present (each tested at alpha = .05), if the omnibus test shows to be statistically significant. Since randomization will be performed in blocks, stratified by region of collaborating center or as external admission, all analyses will include this as a covariate, even though it is not expected this variable will lead to bias. As participants will be randomly assigned to experimental and control condition, no differences across conditions are expected in other study parameters (socio-demographics, alcohol and substance use, medication use, treatment classification, social support and self-compassion). If, however, in contrast to what would be expected, there are significant differences at baseline in any of these parameters across conditions, these will be included as covariate(s) in analyses with primary and secondary outcomes as dependent variable. As ESM data have a multilevel structure, multiple ESM observations (level 1) will be treated as nested within time points (i.e., baseline, post-intervention and 6-month, 18-month, and 24-month follow-up) (level 2) and time points will be treated as nested within subjects (level 3).

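### The stated end of outcome assessment (December 2022) is 7 to 8 months too early for the 24-month follow-up of participants enrolled in June 2021

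*Protocol article*

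**What the plan says.** All statements are in the protocol article.

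- **Study design** places the follow-ups "6, 18 and 24 months after completing the intervention period", with the post-intervention assessment defined as "post-intervention (i.e., after the 6-week intervention period".
- **Statistical analysis** keeps assessors masked "until the last assessment of the last participant at 24-month follow-up". The four-time-point analysis (Wald-type omnibus test, df = 4) is to be run "when data collection for assessments at 24-month follow-up has been completed".
- **Sample size** requires 130 participants (65 per condition) and recruits 174, because "we will allow for a 25% attrition rate at 2-year follow-up".
- **Trial status** gives the calendar: "the first enrollment was in January 2019", then "recruitment was completed in June 2021, and outcome assessment will continue until December 2022".

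No section shortens follow-up for late entrants or sets a common closing date.

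**The concern.** Recruitment closing in June 2021 and assessment ending in December 2022 leave 18 months for the last enrolees, but the design needs 6 weeks plus 24 months. Either the published end date is wrong, or the long-term outcome is cut short for late enrolees and no other section says so.

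The 18- and 24-month outcomes carry the third objective in the Introduction, hypothesis H3 under Secondary outcomes, and the df = 4 analysis. Outcomes made unobservable by a closing date are not attrition, and the 25% allowance was set for loss to follow-up. A team working to the stated date could treat 24-month data collection as complete, and start the long-term analysis, while visits required by the design were still due.

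**Working it through.** **Inputs.** First enrolment January 2019, end of recruitment June 2021 and end of assessment December 2022 (Trial status). Intervention 6 weeks, follow-up counted from its end (Study design). 65 per arm needed, 25% attrition, 174 recruited (Sample size). Only months are given, so the first and last days of each month are used as bounds. The intervention is taken to start at enrolment; any delay would move the visits later.

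**1. The plan's own sample size.** 65 / (1 − 0.25) = 86.7, so 87 per arm and 174 in total. Expected loss is 87 × 0.25 = 21.75, matching the stated 22 or so per condition. The figures reproduce, with the whole inflation assigned to attrition.

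**2. Last visits.** Enrolment + 6 weeks + m months:

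| Enrolled | 6 months | 18 months | 24 months |
|---|---|---|---|
| 1 June 2021 | 13 Jan 2022 | 13 Jan 2023 | 13 July 2023 |
| 30 June 2021 | 11 Feb 2022 | 11 Feb 2023 | 11 Aug 2023 |

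The last 24-month visits fall 7 to 8 calendar months after December 2022. Counting 24 months from enrolment, without the 6 weeks, still gives June 2023. The only combination that gives December 2022 is June 2021 + 18 months from enrolment, which is neither the final time point nor the stated origin. The last 6-month visit is due by February 2022, well inside the stated period.

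**3. Latest enrolment that can reach month 24.** December 2022 − 24 months − 6 weeks = 20 October 2020 (from 1 December) to 19 November 2020 (from 31 December).

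**4. Share affected if December 2022 is the real end.** The accrual pattern is an assumption. Under uniform accrual, share = (end of recruitment − cut-off) / (end of recruitment − first enrolment):

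- Lowest: cut-off 19 November 2020, accrual 1 January 2019 to 1 June 2021: 194 / 882 days = 0.220, or 38 of 174.
- Highest: cut-off 20 October 2020, accrual 31 January 2019 to 30 June 2021: 253 / 881 days = 0.287, or 50 of 174.
- Widest accrual window (1 January 2019 to 30 June 2021), end 31 December 2022: 223 / 911 days = 0.245, or 43 of 174.

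For other shapes, take the widest window, where the cut-off lies at c = 688 / 911 = 0.755 of accrual. A linear rise from zero gives 1 − c² = 0.43; a linear fall to zero gives (1 − c)² = 0.06.

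For the 18-month visit the cut-off is 20 April to 19 May 2021. Uniform accrual then gives about 2% to 8% (3 to 14 participants).

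**5. Observed at 24 months.** With a quarter closed out and 25% attrition in the rest: 174 × 0.75 × 0.75 = 97.9, about 98 (49 per arm), against 130 (65 per arm). Total missing is 1 − 0.75 × 0.75 = 44%, against 25% allowed. At the 6% and 43% extremes: 174 × 0.94 × 0.75 = 123 and 174 × 0.57 × 0.75 = 74.

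**6. Power.** The article's simulation correlations are not given, so 0.82 cannot be reproduced. As a guide, assume SMD 0.3 at all four times, baseline adjustment, and equal correlations of 0.81 (which roughly reproduces the stated 0.87) or 0.5. Use all available data, with 65 per arm at the first three times and either 65 or 49 at month 24:

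| Quantity | Correlation | 65 at month 24 | 49 at month 24 |
|---|---|---|---|
| Omnibus, df = 4 | 0.81 | 0.880 | 0.873 |
| Omnibus, df = 4 | 0.5 | 0.592 | 0.580 |
| 24-month contrast | 0.81 | 0.83 | 0.75 |
| 24-month contrast | 0.5 | 0.51 | 0.42 |

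With 87 per arm at the first two visits, 65 at month 18 and 49 at month 24, the 24-month contrast is 0.78 and 0.43. The omnibus test loses about 0.01; the 24-month contrast loses more.

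**The case against.** The strongest reply is that this is one date in a status note against an otherwise consistent design. Nothing shortens follow-up, and the long-term analysis is conditional on 24-month data collection being complete. A misstated date, perhaps 18 months counted from June 2021, is a simple explanation, though the article does not confirm it. This stands: the article cannot show that any participant will actually go unassessed. It does not remove the contradiction, because no reading of 24 months gives December 2022.

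Three stronger readings are tempting and are not supported.

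- *The long-term power of 0.82 fails.* That figure is for detecting an effect at one or more time points. On the assumptions above the omnibus power barely moves. A larger loss would need an effect concentrated at month 24, which the article does not assume.
- *The 24-month comparison would rest on early enrolees alone.* That is true of the observed month-24 values. The planned REML model also uses earlier visits of people without month 24, so a completers-only calculation with 49 per arm (0.72 at correlation 0.81, 0.40 at 0.5) overstates the loss. Missingness fixed by the calendar is also more benign under missing at random than dropout related to outcome.
- *A quarter of the sample is lost.* This needs both December 2022 as the true end and roughly uniform accrual.

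**Conclusion.** The inconsistency stands and needs no modelling: Study design and Statistical analysis put the last assessment in July to August 2023, and Trial status ends assessment in December 2022.

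The size of the consequence is conditional. It is nil for the data if the date is a slip. If the date is real, 22-29% under uniform accrual, or about 6% to 43% under linear alternatives, could have no 24-month assessment, in addition to attrition. The damage would fall mainly on the precision of the 24-month contrast, with a small loss at 18 months. A reader might infer that the primary result is weakened; it is not, because both primary time points lie well before the stated end for every participant.

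**What to change.** Reconcile Trial status with Study design, Sample size and Statistical analysis, settling the true end date before the four-time-point analysis is run.

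- **If follow-up is complete as designed:** change the end of outcome assessment to about August 2023 (last enrolment + 6 weeks + 24 months) and run the df = 4 analysis only after that. The cost is a one-line correction plus follow-up already in the design.
- **If assessment really stops in December 2022:** state that the 24-month outcome, and for the last enrolees the 18-month outcome, is administratively unobserved for those enrolled after the cut-off. Report these counts by arm separately from attrition. Restate the expected 24-month sample size and the precision of the 24-month contrast from the actual enrolment dates, which are now known. The cost is a wording change and a less favourable statement about month 24.

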## Data Availability

The data resulting from the current study will not be publicly available. The data, protocol, statistical code, and a list of study sites are available from the corresponding author on reasonable request.

## Abbreviations

AE: Adverse event
BCSS: Brief Core Schema Scales
BPRS: Brief Psychiatric Rating Scale
CECA: Childhood Experience of Care and Abuse
CIDI: Composite International Diagnostic Interview
CTQ: Childhood Trauma Questionnaire
DMEC: Data Monitoring and Ethics Committee
EMI: Ecological Momentary Intervention
ESM: Experience Sampling Method
EQ-5D-5L: EuroQol – 5 Dimensions – 5 Level version
K10: Kessler Psychological Distress Scale
MERC: Medical Ethics Review Committee
MUMC: Maastricht University Medical Centre
mHealth: Mobile Health
PANAS: Positive and Negative Affect Scale
RCT: Randomized controlled trial
RBQ: Retrospective Bullying Questionnaire
RSES: Rosenberg Self-Esteem Scale
SELFIE: Ecological momentary intervention for improving self-esteem
SERS: Self-Esteem Rating Scale
SOFAS: Social and Occupational Functioning Assessment Scale
TAU: Treatment as usual
TCI: Temperament and Characteristic Inventory
TiC-P: Trimbos Institute and Institute of Medical Technology Assessment Questionnaire for Costs associated with Psychiatric Illness
TSC: Trial Steering Committee
WHOQOL-BREF: World Health Organization Quality of Life Instrument-Brief
